### Recruitment assessment

A patient recruitment assessment is performed by NHS staff after informed consent has been obtained and within four days prior to planned discharge from hospital, or during routine ESD care. The following data are collected: demographic data, pre-stroke level of EADL (Nottingham EADL Scale [11]), pre-stroke health status (Oxford Handicap Scale [12]), date of hospital admission, date of stroke, stroke type and subtype, National Institute of Health Stroke Scale (NIHSS) [13], comorbidity and pre-stroke resource usage (adaptation of the Client Service Receipt Inventory (CSRI) [14-16]).

### Baseline assessment

A patient baseline assessment is performed by NHS staff at discharge from routine ESD services and immediately prior to randomisation. The following data is collected: date of hospital discharge, date of ESD discharge, Abbreviated Mental Test Score [17], Sheffield Aphasia Screening Test [18], EADL (Nottingham EADL Scale [11]), health status (Oxford Handicap Scale [12]), quality of life (EuroQol EQ-5D [19]) and mood (Hospital Anxiety and Depression Scale [20]).

Carers receive a baseline questionnaire with the study invitation letter. The questionnaire collects the following data: demographic data, quality of life (EuroQol EQ-5D [19]) and carer stress (Caregiver Strain Index [21]).

### Randomisation

Randomisation is by a central independent web-based service hosted by Newcastle University Clinical Trials Unit. Participants are stratified according to stroke service and randomised to either the intervention or control group in a 1:1 ratio using permuted block sequences. Stroke patients and carers are randomised as a single unit.

### Study control treatment

#### Usual care and provision of booklet about stroke care and rehabilitation

Stroke patients in the control group receive usual ESD care with subsequent referral to other rehabilitation services post-discharge from ESD if required and in accordance with usual care. Patients who have ongoing rehabilitation needs following completion of ESD may be referred to a range of services such as neurorehabilitation teams, day hospitals and community rehabilitation services.

In addition, both control and intervention group participants receive the booklet ‘Care after stroke or transient ischaemic attack. Information for patients and their carers’, written by the Intercollegiate Stroke Working Party [22]. It describes what a stroke is, assessment, acute management and rehabilitation. It is based on the National Clinical Guideline for Stroke [6].

### Study intervention treatment

#### Extended stroke rehabilitation service and provision of booklet about stroke care and rehabilitation

Stroke patients in the intervention group receive an extended stroke rehabilitation service for 18 months following completion of rehabilitation with their ESD team. This is in addition to usual care. They also receive the Intercollegiate Stroke Working Party booklet about stroke care and rehabilitation.

The extended stroke rehabilitation service consists of reviews by a designated senior member of the ESD team at 1, 3, 6, 12 and 18 months post-discharge from routine ESD. We have chosen to evaluate a model where care is coordinated rather than delivered by a senior member of the ESD team, as this model could potentially be delivered by the National Health Service (NHS) throughout the UK, if shown to be effective. The role of specialists coordinating rather than delivering rehabilitation has been shown to be effective in other conditions [23].

Each review consists of:A semi-structured interview to identify the patient’s progress, current rehabilitation needs and service provision. The interview addresses everyday activities (personal care, meal times, domestic activities, indoor mobility, outdoor mobility, shopping, hobbies and driving), social participation and wider issues (mood, memory, pain, communication and medical issues) which may be problematic for stroke survivors. The views of both the patient and carer (where appropriate) are sought.Joint rehabilitation goal setting. From the identified progress and rehabilitation needs, up to five individual rehabilitation goals are set by the patient (and carer) in collaboration with the senior ESD team member who conducts the review. The focus of joint goal setting is upon increasing participation in everyday activities. The physical, psychological and social factors which may impact on goal attainment are considered. At each review, progress towards goals from the previous review is assessed prior to further goal setting. Achievement of goals is recorded using a Goal Attainment Scale [24].Action planning. The patient (and carer) agree an action plan for each rehabilitation goal. This may include:Verbal advice and encouragement;Discussion with the stroke team, rehabilitation team, primary care team or social services involved in care;Signposting to local activities, community organisations or voluntary services;Referral to stroke services, rehabilitation services or primary care services for further assessment and treatment, if required, according to local guidelines and/or service provision.

The majority of the reviews are intended to be done by telephone. The senior ESD team member will know the patient and carer as he or she will have treated the patient as part of the ESD service. However, if the patient and/or carer is unable to participate in a telephone review, a home visit can be undertaken. Patients are given a study appointment card which also contains a short checklist of rehabilitation issues to be covered in each review. This is to allow patients (and carers) time to consider the topics to be discussed prior to the interview. Patients with aphasia receive an easy access version of the appointment card.

All senior ESD staff taking part in the trial receive an extended stroke rehabilitation service manual and training in delivery of the new service. The extended stroke rehabilitation manual describes how to conduct the reviews, including guidance on exploring rehabilitation needs, goal setting and appropriate interventions to meet a patient’s needs.

Subsequent to each review the ESD therapist or nurse may contact services currently involved in the patients care to discuss progress, goals and care plan.

A summary of the review and recommendations for rehabilitation is sent to the patient, patient’s GP, stroke physician and therapists currently involved in the patient’s care. Patients with aphasia receive an easy access version of the letter.

### Outcome assessments

Outcomes are assessed at 12 months (+/− 7 days) and 24 months (+/− 7 days) following randomisation.

Patient outcome assessments are undertaken by telephone by a researcher based in the study coordinating centre. For participants who do not have a telephone or who are unable to communicate by telephone, outcomes are collected by postal questionnaire. If a patient is unable to participate in a telephone interview or complete a postal questionnaire, outcome assessments are undertaken by local staff trained by the study team.

The following data is collected from patients: EADL (Nottingham EADL Scale [11]), health status (Oxford Handicap Scale [12]), quality of life (Euroqol EQ-5D [19]), mood (Hospital Anxiety and Depression Scale [20]), experience of services (adaption of an experience survey designed by Northumbria Healthcare NHS Foundation Trust) and resource utilisation (adaptation of the CSRI [14-16]).

Carers’ outcome assessments are undertaken by postal questionnaire. This is because the Caregiver Strain Index asks some sensitive questions about the impact of stroke upon the carer [21]; a carer may modify their answer if they could be overheard on the telephone by the patient. The carer outcome questionnaire collects the following data: quality of life (EuroQoL EQ-5D [19]), carer stress (Caregiver Strain Index [21]) and experience of services (adaption of an experience survey designed by Northumbria Healthcare NHS Foundation Trust).

### Blinding

Due to the nature of the intervention, it is not possible to blind stroke patients or carers to treatment allocation. Where patient outcome assessments are undertaken by telephone or face to face, it is intended that they are conducted blinded to treatment allocation. After each assessment the assessor is asked to record whether they have unintentionally become aware of treatment allocation due to conversation with the participant. Success of patient outcome assessment blinding will be reported.

### Study withdrawal

No specific study withdrawal criteria have been pre-set. Stroke patients and/or carers may withdraw from the study at any time for any reason. Data collected prior to withdrawal will be used in the study analysis unless consent for this is specifically withdrawn. Reasons for withdrawal are sought, but patients and/or carers can chose to withdraw without providing an explanation. Investigators, senior ESD team members and/or a patient’s consultee (in the case of mental incapacity) may also withdraw participants from the study at any time if they feel it is no longer in their interest to continue, for example, because of intercurrent illness or adverse events.

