ESD services offer patients the opportunity to continue rehabilitation in their own home following a period of stroke unit care. ESD provided by a specialist multidisciplinary team leads to better clinical outcomes, increased satisfaction with care and reduced NHS costs [3]. ESD is a core component of an evidence-based stroke service, and it is the current ‘gold standard’ for an early community rehabilitation service for stroke patients with ongoing rehabilitation needs who are discharged to their own homes [10]. Typically, an ESD team becomes involved with discharge planning with patient, family and stroke unit staff at an early stage of admission. Prior to discharge from hospital, a member of the team may undertake a home visit (with the patient) or an environmental visit (without the patient). Rehabilitation and ongoing care provided by a specialist ESD team begins immediately after discharge. The duration and intensity of ESD therapy depends upon patient need. The discharge policy of ESD services varies, with some services defining a maximum period of input of three months. ESD teams do not usually retain any contact or involvement with patients once their input has ceased. Following discharge from ESD services, the concept of organised stroke care disappears. Patients who have ongoing rehabilitation needs may be referred to a range of services, most of which do not offer specialist stroke rehabilitation, such as neurorehabilitation teams, day hospitals and community rehabilitation services. This research study is evaluating an extended stroke rehabilitation service which commences when ESD ends. The service is delivered by existing ESD teams and extends organised stroke care beyond ESD.

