### Statistical analysis

#### Primary analysis

The primary outcome is the Nottingham EADL score [11] at 24 months. Analysis will be on the basis of intention to treat. Mean scores will be compared between intervention and control groups using multiple linear regression, including terms for sites and patient-level covariates such as baseline scores.

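### Staff may withdraw patients from the study, not just from the reviews, and after randomisation this route is likelier in the intervention arm, so sicker patients can drop out of the 24-month comparison unevenly

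*Protocol article*

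**What the plan says.** All references are to the protocol article.

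- **Study withdrawal.** The section opens with "No specific study withdrawal criteria have been pre-set". Patients and carers may leave at any time for any reason, and then "Data collected prior to withdrawal will be used in the study analysis unless consent for this is specifically withdrawn". Investigators, senior ESD team members and, for patients lacking capacity, consultees "may also withdraw participants from the study at any time if they feel it is no longer in their interest to continue". The examples given are "for example, because of intercurrent illness or adverse events". Ending the reviews is not distinguished from ending outcome follow-up.
- **Baseline assessment.** This is done "at discharge from routine ESD services and immediately prior to randomisation", so all time after randomisation falls after routine ESD has ended.
- **Study intervention treatment.** The intervention arm receives "reviews by a designated senior member of the ESD team at 1, 3, 6, 12 and 18 months post-discharge from routine ESD".
- **Background.** On routine services, the article says that "ESD teams do not usually retain any contact or involvement with patients once their input has ceased". The control arm receives usual care.
- **Outcome assessments.** Patient outcomes at 12 and 24 months are collected mainly by telephone from the coordinating centre, with postal and local-staff alternatives.
- **Primary analysis.** The outcome is the NEADL at 24 months, compared by linear regression with terms for site and covariates such as baseline score. "Analysis will be on the basis of intention to treat".

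**The concern.** The staff who may withdraw a patient include those who deliver the intervention. They know the allocation, and after randomisation they have five scheduled occasions to notice illness in one arm and usually none in the other. The example triggers, illness and adverse events, are likely to go with a low NEADL score. If such a withdrawal ends follow-up, the 24-month outcome is lost, because even the last review (18 months) comes before it.

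The loss would then depend both on arm and on prognosis. The remaining intervention patients would look better than the arm as randomised, while equally ill controls would more often stay in. Covariates measured at baseline cannot correct for a trigger that arises later. Analysing patients in their randomised groups cannot restore a score that was never collected. The 25% attrition allowance protects power, not balance between the arms.

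**Working it through.** **1. The plan's own figures.** Inputs from Sample size and the Abstract: difference 6, SD 18, power 90%, 5% significance (two-sided assumed), equal arms, 25% attrition.

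- Normal approximation: n per arm = 2 × 18² × (1.960 + 1.282)² / 6² ≈ 189.1, rounded up to 190, or 380 in total.
- With the t distribution, power is 0.8999 at 190 per arm and 0.9013 at 191 per arm, so 191 per arm gives the stated 382.
- 382 / 0.75 = 509.3, rounded up to 510.

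The sample size reproduces. It is not in dispute.

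**2. The routes out after randomisation.**

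| Route | Intervention | Control |
|---|---|---|
| Patient or carer choice | yes | yes |
| Consultee, if capacity is lacking | yes | yes |
| Investigator | yes | yes |
| Senior ESD team member | yes, with five scheduled reviews | permitted, but usually no contact to prompt it |

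Only the last route differs by design. Before randomisation the ESD team treats every participant and no allocation exists, so withdrawals in that period cannot bias the comparison.

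**3. Illustrative size.** Let p be the share of intervention patients withdrawn by staff who would otherwise have given a 24-month score. Let g be how far their mean would lie below that of the remaining patients. Assume no matching loss among controls. The full-arm mean is then the remaining mean minus p × g, so the observed difference is inflated by

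bias = p × g.

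Neither p nor g is in the document; the values below are assumptions. The standard error is 18 × √(2/191) = 1.84. The two-sided type I error is Φ(bias/SE − 1.96) + Φ(−bias/SE − 1.96).

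| p | g (points) | Bias (points) | Share of 6-point target | Type I error |
|---|---|---|---|---|
| 3% | 10 | 0.30 | 5% | about 5% |
| 5% | 15 | 0.75 | 12.5% | about 7% |
| 10% | 15 | 1.50 | 25% | about 13% |
| 10% | 20 | 2.00 | 33% | about 19% |

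For the third row: 1.50/1.84 = 0.81, and Φ(−1.15) + Φ(−2.77) ≈ 0.129.

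**4. Sensitivity to the definition of the gap.** If g is measured from the full-arm mean instead, bias = p × g / (1 − p). With p from 2% to 10% and g from 9 to 27 points, this runs from 0.02 × 9 / 0.98 = 0.18 to 0.10 × 27 / 0.90 = 3.0 points.

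**5. If outcomes are still sought.** This source of bias disappears, except where the patient declines, cannot be reached or has died.

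**The case against.** The case on the other side has real force on several points.

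- **Withdrawal is not confined to one arm.** Investigators and consultees can withdraw controls, and the Background sentence describes what ESD teams usually do in routine services; it is not a trial rule. A reader might infer that ESD staff have no contact at all with controls, or that only intervention patients can be withdrawn. The document supports neither. It supports a difference in opportunity.
- **Part of the clause's use is harmless.** Several weeks may pass between recruitment and randomisation, and up to 15% may drop out in that time. The clause draws no line at randomisation, so some withdrawals under it will precede allocation. It also allows withdrawal at any time, so the later period remains exposed.
- **Loss of the 24-month score is a reading of the text.** The sentence on data retention follows the one on patients and carers and precedes the staff clause, and it does not say that collection stops. Still, withdrawal is from the study, and nothing provides for later data.
- **Intention to treat is not contradicted.** A reader might infer a direct conflict with the analysis statement. That statement fixes comparison by randomised group; withdrawal creates missing data, whose handling may be set out in an analysis plan that is not shown. But no analysis can recover uncollected scores without untestable assumptions, and the concern is a stated rule that governs collection.
- **The size is assumed.** Some of these patients would have died or not responded in either arm, within the planned 25%. That lowers p but does not remove the mechanism.

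**Conclusion.** The point holds as a risk written into the withdrawal rule, not as a demonstrated bias. As worded, the rule lets unblinded staff with much more contact with one arm remove ill patients from the study, and it makes no provision for collecting their 24-month outcome. This undermines the intention-to-treat analysis, and the likely direction favours the extended service.

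The size cannot be derived from the document. The illustration of 0.3-2.0 points, or 5-33% of the target difference, rests on 3-10% of the intervention arm being withdrawn by staff, a 10-20 point gap from the remaining patients, no matching loss of controls, and every withdrawn patient otherwise giving a score. A reader might take the 13% type I error as an estimate for this trial. It is not: it is the result for one assumed pair, 10% and 15 points. At the low end the effect is negligible. The case for acting is that the loss is avoidable and cannot be made good once the 24-month window has passed.

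**What to change.** In Study withdrawal, state that after randomisation a staff decision that a participant should not continue with the reviews does not by itself end outcome follow-up. The 12- and 24-month outcomes are then sought for every randomised patient unless the patient or consultee declines.

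Record two separate dispositions, stopped reviews and withdrew from follow-up, and report each by arm, initiator and reason. Keep patients who only stopped reviews in the intention-to-treat analysis. For patients already withdrawn by staff alone, seek the outcomes where consent allows.

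This concerns outcome data collection only and sets no rule on when reviews should stop. The cost is a short amendment and a note to the centres. The outcome assessments are already planned, mostly run centrally and independent of the ESD teams. Trial status shows recruitment still open in February 2015 and follow-up running until 2017, so at that point the change could still take effect.

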### Safety evaluation

The safety of the extended stroke rehabilitation service is being evaluated by examining the occurrence of all adverse events and serious adverse events in accordance with National Research Ethics Committee (NRES) guidance.

### Statistical analysis

#### Primary analysis

The primary outcome is the Nottingham EADL score [11] at 24 months. Analysis will be on the basis of intention to treat. Mean scores will be compared between intervention and control groups using multiple linear regression, including terms for sites and patient-level covariates such as baseline scores.

#### Secondary analyses

Secondary outcomes will be compared between intervention and control groups using multiple linear regression, including terms for sites and patient-level covariates such as baseline scores. Further exploratory descriptive analyses will examine the impact of the severity of activity limitation, pre-stroke health status and comorbidity upon the effectiveness of the intervention; there is not sufficient power to perform any formal subgroup analyses.

#### Sample size

There is consensus that a difference of 6 points (range: 0 to 66, standard deviation (SD): 18) on the Nottingham EADL Scale is clinically important, and power calculations for previous multicentre rehabilitation trials have been based upon this difference [16,25]. Responses from 382 patients split equally between intervention and control groups will provide 90% power to detect a difference in mean Nottingham EADL score of 6 points. Based on attrition in other stroke rehabilitation trials, we believe that there may be up to 25% attrition between study randomisation and the 24-month (primary) outcome assessment. To allow for this, we aim to randomise 510 participants into the study.

Although participants may be recruited any time from within four days prior to discharge from hospital until discharge from ESD, many are likely to be recruited prior to discharge from hospital. There may be several weeks between recruitment and randomisation, and some participants may withdraw from the study during this time. Our current estimate is that up to 15% may drop out before randomisation. The target recruitment sample size is being kept under review, and recruitment will cease when we estimate that 510 participants will be randomised. Reasons for loss from the trial are recorded.

### Economic analysis

The economic evaluation will include both a cost-effectiveness analysis (CEA) and a cost-utility analysis (CUA) [26]. The CEA will be undertaken using the Nottingham EADL Scale [11] at 24 months as the measure of effect. The result of the CEA will be an incremental cost-effectiveness ratio (ICER) [27]. In order to quantify the uncertainty associated with the ICER, the stochastic analysis will be conducted, with the results presented as a cost-effectiveness acceptability curve (CEAC) [28]. The CEAC will show the probability that an extended stroke rehabilitation service is cost effective compared with usual post-ESD care, given the observed data, for a range of maximum monetary values that decision-makers may be prepared to pay for unit change in Nottingham EADL Scale [11]. The CUA will compare changes in health-related quality of life, based on responses to the EuroQoL EQ-5D [19], at baseline and 24 months across both arms of the trial. These data will be combined with study participant’s mortality to estimate quality-adjusted life years (QALYs). Both costs and QALY data will be combined into an incremental cost per QALY. Both analyses will be carried out from the perspective of the NHS, but we will also take societal perspective by including costs borne by the participants themselves and their informal carers by obtaining information about time away from employment and time spent providing care.

Resource utilisation will be assessed at 12 and 24 months using an appropriate adaptation of the CSRI [14-16]. We will identify all the relevant financial costs associated with providing the intervention. Relevant costs will be categorised as either fixed costs or variable costs, where fixed costs are those resources that are required to set up and run the service and variable costs are those required to treat an individual patient. Where appropriate, discounting [26] will be applied to financial costs and outcomes. Financial costs will be attached to the items of service used using data from the Personal Social Services Research Unit [29]. Because the consequences of an extended stroke rehabilitation service may extend beyond the 24-month timeframe of the trial, and may have on-going significant financial cost and quality of life implications (for example, a reduced incidence of hospitalisation related to falls or need for residential or nursing home care), a Markov model will be developed that can be used to predict outcomes up to 60 months based on the status at 24 months. Transition probabilities and cost associated with each state in the model will be obtained from published literature and, where no published evidence exists, expert opinion will be sought. Other forms of uncertainty such as variation in unit prices will be explored within the deterministic sensitivity analyses; where appropriate these CEACs will also be produced for these analyses.

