## Methods/design

### Study aim and objectives

This study aims to determine the clinical and cost effectiveness of an extended stroke rehabilitation service. The objectives of the study are as follows:To determine whether an extended stroke rehabilitation service (intervention) improves patient outcomes compared to usual care (control). The primary outcome is extended activities of daily living (EADL) at 24 months following randomisation. Secondary outcomes are: health status, quality of life, mood and experience of services (12 and 24 months following randomisation).To determine whether an extended stroke rehabilitation service improves carer outcomes compared to usual care. Outcomes are: quality of life, carer stress and experience of services (12 and 24 months following randomisation).To determine the cost effectiveness of an extended stroke rehabilitation service.To document how the extended stroke rehabilitation service is implemented and delivered in different settings.To seek the views and experiences of patients, carers and rehabilitation staff about the community rehabilitation they have received or provided.To explore the impact of the severity of activity limitation, pre-stroke heath status and comorbidity upon the effectiveness of the intervention.

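### The cost-utility analysis names EQ-5D at baseline and 24 months as the source of its QALYs, although patients also complete EQ-5D at 12 months

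*Protocol article*

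**What the plan says.** The Economic analysis section of the protocol article describes the cost-utility analysis in three steps.

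- Utility data: "The CUA will compare changes in health-related quality of life, based on responses to the EuroQoL EQ-5D [19], at baseline and 24 months".
- QALYs: those data are joined with participants' "mortality to estimate quality-adjusted life years (QALYs").
- Result: "Both costs and QALY data will be combined into an incremental cost per QALY".

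The trial collects more utility data than this. Under Baseline assessment, patients give "quality of life (EuroQol EQ-5D [19]) and mood (Hospital Anxiety and Depression Scale [20"]) just before randomisation. Study aim and objectives lists patient quality of life at two follow-ups: "Secondary outcomes are: health status, quality of life, mood and experience of services (12 and 24 months following randomisation"). Outcome assessments, which covers the 12- and 24-month contacts, confirms the instrument: "quality of life (Euroqol EQ-5D [19]), mood (Hospital Anxiety and Depression Scale [20]), experience of services".

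On the cost side, the same economic section uses both follow-ups: "Resource utilisation will be assessed at 12 and 24 months using an appropriate adaptation of the CSRI [14-16"]). Nowhere does the article bring the 12-month EQ-5D into the QALY.

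**The concern.** A QALY is the area under a utility curve over time. Two measurements 24 months apart describe that curve by a straight line. A third measurement halfway along is already being taken, and the sentence on the cost-utility analysis leaves it out. Costs would then rest on both follow-up contacts and QALYs on one.

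The design gives a reason to want the middle point. Under Study intervention treatment, reviews take place at 1, 3, 6, 12 and 18 months after ESD discharge, so four of the five fall in the first year and the service ends before the 24-month measurement. The between-arm difference could rise early, fade late, build up steadily or appear late. Two end points cannot tell these shapes apart.

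What is at stake is the denominator of the cost per QALY. Cost effectiveness is part of the stated aim, and the Discussion says the results are to inform service planning. In addition, a patient who completes 12 months and is then lost to follow-up has an observed EQ-5D that the stated calculation does not use.

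**Working it through.** **Plan's own figure.** The article states no utility effect and no QALY value, so there is none to reproduce. All utility differences below are assumptions.

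**Inputs from the article.** EQ-5D at 0, 12 and 24 months (Baseline assessment; Outcome assessments); time points named for the cost-utility analysis, 0 and 24 months (Economic analysis); horizon 2 years.

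**Formulas.** Let d0, d12 and d24 be the between-arm differences in mean EQ-5D utility, without discounting and leaving deaths aside.

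- Two points: 2 × (d0 + d24)/2 = d0 + d24.
- Three points: 1 × (d0 + d12)/2 + 1 × (d12 + d24)/2 = d0/2 + d12 + d24/2.
- Gap, three-point minus two-point: d12 - (d0 + d24)/2.

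The gap is zero exactly when d12 is the average of d0 and d24.

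**Numbers.** With d0 = 0 and the same incremental cost in both calculations, the two-point cost per QALY divided by the three-point one equals the three-point gain divided by the two-point gain.

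| Assumed shape | d12 | d24 | Two-point gain | Three-point gain | Gap | Ratio of cost per QALY |
|---|---|---|---|---|---|---|
| Linear | 0.02 | 0.04 | 0.040 | 0.040 | 0 | 1.0 |
| Early, sustained | 0.04 | 0.04 | 0.040 | 0.060 | 0.020 | 1.5 |
| Early, half lost | 0.04 | 0.02 | 0.020 | 0.050 | 0.030 | 2.5 |
| Early, gone by 24 months | 0.04 | 0 | 0 | 0.040 | 0.040 | undefined |
| Late | 0 | 0.04 | 0.040 | 0.020 | -0.020 | 0.5 |

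**Range.** The gaps scale with the assumed effect, and the ratios do not change. For a sustained effect of 0.03, 0.05 or 0.10, the gap is 0.015, 0.025 or 0.050 and the ratio stays at 1.5.

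**Limits of the two calculations.**

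- Non-linearity alone does not produce a gap. A linear rise to 0.05 with an S-shaped wave added around it, balanced about 12 months, has true area 0.050, and both calculations return 0.050. Curvature that is the same in both arms cancels.
- Three points are not exact either. Take a difference that reaches 0.05 at month 3, holds to month 18 and falls in a straight line to 0 at month 24. The true area is 0.25 × 0.05/2 + 1.25 × 0.05 + 0.5 × 0.05/2 = 0.081. Three points give 0.050 and two points give 0.

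**Loss to follow-up.** The Sample size section allows up to 25% attrition by 24 months, about 128 of 510 (510 - 382). The article does not say how many of these would have reached the 12-month assessment, so the number of unused EQ-5D responses cannot be computed.

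**The case against.** The strongest reply is that a journal article condenses the full protocol. It gives no QALY formula, does not state a straight-line assumption and does not say that 12-month EQ-5D is excluded. A fuller economic plan may use all three points. This is fair as far as it goes: the exclusion is read from the time points named. But the article is not silent on them. It names two for the utility data and derives the QALYs from those data, while naming both follow-ups for costs in the same section. If a fuller plan uses three points, the published sentence disagrees with it and still needs correcting.

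Several stronger readings are tempting and are not supported.

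- A reader might infer that the QALY is wrong whenever the benefit is not a straight line. The formula shows otherwise: what matters is where the 12-month between-arm difference lies relative to the average of the other two.
- A reader might infer that the acceptability curve is distorted. The curve described in the Economic analysis section is expressed per unit change in the Nottingham EADL Scale, so it belongs to the cost-effectiveness analysis. No QALY-based curve is described in that passage.
- A reader might infer that patients who die after 12 months drop out of the QALY. Mortality is already part of the calculation; only the point about living patients lost to follow-up stands.
- A reader might infer that the benefit will peak early and fade. The article does not say so. Reviews run to 18 months, which fits a cumulative gain equally well, and the economic section allows for consequences beyond 24 months.
- A reader might infer that comparing changes rules out baseline adjustment. It does not. Secondary analyses adjusts secondary outcomes for site and baseline scores, and doing the same for QALYs is a matter of precision.

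**Conclusion.** The point holds in a limited form. The article fixes the cost-utility analysis on EQ-5D at baseline and 24 months while the trial also collects it at 12 months. Followed as written, the incremental QALY departs from the three-point value by d12 - (d0 + d24)/2.

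The size cannot be derived from the article. Under the assumed shapes, the two-point cost per QALY runs from 0.5 to 2.5 times the three-point one, equals it for a linear difference, and is undefined if the difference has gone by 24 months. These factors assume no baseline difference, equal incremental costs, no discounting and the same treatment of deaths in both calculations.

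The weight is moderate. Only the cost per QALY is affected; the primary outcome, its analysis, the sample size and the Nottingham EADL cost-effectiveness analysis with its acceptability curve are not. The 12-month data are collected in any case, so nothing is lost beyond repair.

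**What to change.** Reword the cost-utility sentence so that QALYs are the area under each patient's EQ-5D utility curve through baseline, 12 and 24 months, combined with mortality by date of death. State that the between-arm QALY difference is estimated with adjustment for baseline EQ-5D and site. How a missing 24-month value is handled for patients with a 12-month response can be left to the analysis plan.

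The cost is one sentence and no new data. It should be settled before outcome data are examined by arm, so that the choice of time points cannot be linked to the result. If a fuller economic plan already specifies three points, the change only brings the published text into line. Three points reduce the error from an uneven benefit but need not remove it, and the report should say so.
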